## Data Management

During the study, all data assessed will be electronically saved. The saved data will be securely stored by password and pseudo-randomization. All data will be subjected to medical confidentiality and general data protection regulations.

## Data Analysis

All statistical analyses will be performed using SPSS software version 25 (SPSS INC., Chicago, IL, USA). Sociodemographic data, chronotype, diary data and blood parameters will be reported in form of descriptive statistics. Continuous variables will be presented as mean ± *SD* and normality of continuous data will be measured by using the Kolmogorov-Smirnov-Test. Accordingly, we will use parametric and non-parametric analyses. For all calculations, the significance level will be determined at α < 0.05.

Data analysis will be performed according to intention-to-treat analysis (ITT) rules. In particular, this means that all subjects who completed the questionnaires of the first session and the 1st week of the diaries are included in the analysis, regardless of whether their subsequent data sets are complete or whether they have dropped out of the study. This is done by imputing missing data with the help of all available data that was assessed until then. Participants who withdraw their consent and were not assessed with baseline measurements will be treated as dropouts. All other subjects regardless from the study condition will be analyzed according to ITT.

The data will be evaluated in three different ways: First, outcomes of the endpoint of the study will be compared between the intervention and control groups using unpaired group analyses (e.g., Student's *t*-test, Mann-Whitney *U*-test, Kruskal-Wallis test, one-way ANOVA). Secondly, within-subject analyses of the intervention and control groups are performed, comparing the changes between the start and end of the study of the two groups (e.g., two-way ANOVA). Thirdly, the data are calculated independently of group membership in two-dimensional linear regression using the Routine Variability Scores as an independent variant.

Additionally, statistical differences in the frequency of dropouts between the two groups are calculated using chi-square tests and survival analyses. Multiple regression analyses will be applied to investigate the degree to which predictor variables (i.e., Routine Variability Scores, depression level, severity of alcohol consumption behavior, and self-efficacy score) contribute to outcomes of primary and secondary measures.

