## Abstract

**Background:** Hallmarks of alcohol use disorder (AUD) are disturbances of circadian rhythms and everyday structures. While circadian rhythms dictate the timing of daily recurring activities such as sleep, activity, and meals, conversely, these activities represent time cues, so called *Zeitgebers*, that the circadian system uses to synchronize with the environment. Here we present a study protocol for our newly developed therapy approach for AUD patients, in which we take advantage of this mutual influence and stabilize and strengthen their circadian system by creating strict daily schedules for daily *Zeitgeber* activities. Since every person has a circadian system with its own characteristics and is subject to social obligations, the daily plans are personalized for each test person. Our hypothesis is that a regular exposure to *Zeitgebers* stabilizes behavioral and physiological circadian rhythms and thereby reduces the risk of alcohol relapses and depressive symptoms and facilitates physical recovery in AUD patients during the 1st weeks of their addiction therapy.

**Methods/design:** The study is a 6-weeks single site trial with a controlled, randomized, single-blinded, parallel-group design including patients with a diagnosis of AUD. The study runs parallel to the standard addiction therapy of the clinic. Patients are randomly assigned to either an intervention group (DAILY) or a sham control group (placebo treatment). Questionnaires and physiological assessments of both groups are conducted before and immediately after the intervention or control treatment. According to our hypothesis, the primary outcomes of this study are improvements of regularity, alcohol consumption, and relapse rate in AUD patients compared to AUD patients receiving control treatment. Secondary outcomes are reduced depressive symptoms and increased physical recovery.

**Discussion:** This study is a randomized controlled trial to investigate the efficacy of a personalized circadian *Zeitgeber* therapy as an adjunctive treatment for alcohol use disorder patients. The overall goal of this and more extended future studies is the development of an adjunctive therapy for AUD patients that is uncomplicated in its use and easy to implement in the clinical and everyday routine.

**Trial registration:** This study is registered at the German Clinical Trial Register with the trial number DRKS00019093 on November 28, 2019.

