## Study Design

### Design

The study is a 6-weeks trial with a controlled, randomized, single-blinded, parallel-group design including patients with a diagnosis of AUD. Patients are randomly assigned to either an intervention group (DAILY) or a sham control group (placebo treatment). As this study represents a pilot randomized trial, which does not primarily focus on proving treatment successes but more on ascertaining the best options for the future main trial, we will include each eligible patient within this year instead of using formal power calculations (64).

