### Study Population

Men and women, unemployed and employed subjects are equally included in the study. Depending on whether the subjects are patients of the ward or day clinic, they are in detoxification or post-detoxification treatment. Study enrollment of subjects who are newly admitted to the detoxification program of the ward will take place at the earliest after 5 days of detoxification, to exclude cognitive and physical limitations caused by acute intoxication and its after-effects. Study participants who are discharged from the ward either go home, receive further treatment in the day clinic, or go to other institutions for long-term therapy. Study participants who are discharged from the day clinic either go home after discharge or go to other institutions for further treatment. The health conditions of all test persons allow them to perform their daily tasks without external assistance. Approximately half of the study subjects have a regular job, while the others are unemployed or retired. Usually 3–5 subjects are involved in the study simultaneously.

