## Measured Outcomes

Our primary hypothesis is that a regular exposure to *Zeitgebers* stabilizes circadian behavioral rhythms and thereby reduces the risk of alcohol relapses in AUD patients. Therefore, the first primary outcomes of the study are the Routine Variability Score and drinking behavior of each individual test person. For generation of the Routine Variability Scores, first, day-to-day variability will be calculated from the following parameters: bedtime, wake-up time, sleep quality, time of getting-up in the morning, time to go to bed in the evening, lights-off time, breakfast time, lunch time and dinner time. The individual Routine Variability Score is comparable to the validated social rhythm metric scale (SRMS) (66) and will be calculated as follows (example for bedtime): For the period of 1 week, the average bedtime will be calculated. Then the deviation from this average bedtime is calculated in minutes for each day. These deviations are summed up and the mean value is calculated. This mean value will be coded according to the magnitude of time variability: 1: 0–15 min, 2: 16–30 min, 3: 31–45 min, 4: 46–60 min, 5: 61–75 min, 6: 76–90 min, 7: 91–105 min, 8: 106–120 min, 9: 2–3 h, 10: 3–4 h, 11: over 4 h (67). This way a separate score can be created for each parameter collected in the diary. These scores can be calculated on a weekly basis to examine whether relapses or deterioration in well-being are related to irregularities in the daily routine during that week, or over the duration of the entire survey phase to check how regularity over a longer period is related to drinking behavior and well-being. In addition, the scores for sleep and meals, for example, can be calculated individually to examine their influence on drinking behavior and well-being separately.

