### Limitations

At this state, however, DAILY has some limitations as it is designed as a pilot study and so, it aims primarily at proofing the principle study concept and the overall impact of a daily structure therapy in AUD patients. A limitation of the current design is that it does not include objective physiological and behavioral measures of circadian rhythm improvement such as (e.g., melatonin rhythms or actigraphy, but only focuses on more subjective behavioral rhythms based on diary entries). However, the primary aim of this pilot study is the proof whether a therapeutic approach to improve sleep hygiene and regularity in daily routine can generally improve AUD symptoms.

Furthermore, inpatients and semi-inpatients are included into our study. Inpatients and semi-inpatients usually already have a more structured daily routine than outpatients since they are given a regulated daily structure by the clinical routines and the fixed therapy hours. Therefore, the determination of individual circadian preferences and characteristics might be limited. However, in our clinic, where the study is currently taking place, patients have no mandatory eating or sleeping hours and can leave the ward and day clinic outside therapy hours. Thus, the test persons can in principle follow their own rhythms, which is often taken advantage of, especially for food and snacks in the surrounding areas. Nevertheless, many test persons report that they generally have more structured daily routines in the clinic than at home, as they adapt to the rhythms of their fellow patients as well as the rhythms of the clinic meals offered.

Furthermore, there are also test persons who, after detoxification or after their stay in the day clinic, go for further treatment to other clinics where they are integrated into a daily structure. Since this daily structure does not necessarily correspond to the subject's circadian characteristics, the analysis of pilot data must consider that these test persons cannot always independently follow the daily schedule during the study. Accordingly, it is possible that the implementation of the DAILY program is more suitable for clinics from which patients are usually discharged home.

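### Several primary outcomes, each with several possible measures, are all tested at 0.05 with none ranked first, and the article does not settle whether a significant result counts as proof

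*Protocol article*

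**What the plan says.** All of this is in the protocol article.

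- **Primary outcomes.** The Abstract says "the primary outcomes of this study are improvements of regularity, alcohol consumption, and relapse rate in AUD patients". Study Hypotheses and Objectives covers the same three domains. Measured Outcomes says "the first primary outcomes of the study are the Routine Variability Score and drinking behavior of each individual test person".
- **Measures of regularity.** Measured Outcomes builds the Routine Variability Score from nine diary parameters, beginning "bedtime, wake-up time, sleep quality, time of getting-up in the morning". It allows a separate score for each parameter, by week or over the whole diary phase.
- **Measures of drinking.** AUDIT, EuropASI, number of drinks (Timeline Followback, TLFB-30) and alcohol-free days (TLFB-30) are listed. Relapse is a primary outcome without a definition of its own. The diary also records daily craving.
- **Analysis.** Data Analysis says "The data will be evaluated in three different ways": the arms compared at the endpoint, the change from start to end compared, and regression on the Routine Variability Scores regardless of arm. For the level it says "For all calculations, the significance level will be determined at α < 0.05".
- **Aim.** Design says the pilot "does not primarily focus on proving treatment successes but more on ascertaining the best options for the future main trial" and forgoes a power calculation. Limitations says "the primary aim of this pilot study is the proof whether a therapeutic approach to improve sleep hygiene and regularity" can generally improve symptoms of alcohol use disorder. The Abstract describes a randomized trial of efficacy.

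**The concern.** A 0.05 level limits the error of one test. Here it applies to every test, with several primary outcomes, several candidate measures for each, and two ways of comparing the arms. Nothing in the article says which result decides the question. A reader who takes the Limitations wording at its word could treat any one significant primary test as proof. A reader who takes the Design wording at its word would treat none of them so.

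The regularity outcome adds a separate difficulty. DAILY instructs participants to be regular. The week 2 section says the planned times are written by hand into the diary pages, and the same diary yields the score. Controls get no such times. A between-arm difference on this score is therefore expected if participants follow instructions, or simply copy the written times. By itself it says nothing about drinking, yet under the present wording it would be a positive primary outcome.

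At stake is what the pilot passes on to the main trial: a significant result picked from many, or estimates that can be used for planning.

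**Working it through.** The article gives no sample size, power or overall error rate, so there is no figure of its own to reproduce. The check is how far the stated rule lets the overall error rise when DAILY has no effect.

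**Inputs from the article**
- Level per test: 0.05 (Data Analysis). Two-sided testing is assumed, because sidedness is not stated.
- Primary outcomes: 3 (Abstract).
- Drinking measures: AUDIT, EuropASI, TLFB-30 drinks, TLFB-30 alcohol-free days, relapse = 5. Counting craving as well would make 6.
- Diary scores: 9. Total 9 + 5 = 14.
- Between-group routes: 2 (endpoint, change). The third route ignores allocation and is left out.

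**Assumption.** The article gives no correlations. A common correlation between measures of 0 to 0.7 is used, with test statistics treated as normal.

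**Formula, independent tests, one route.** Chance of at least one p < 0.05 in either direction = 1 − 0.95^k. In DAILY's favour only, each test has a 2.5% chance, so it is 1 − 0.975^k.

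- k = 3: 1 − 0.95^3 = 0.143; in favour, 1 − 0.975^3 = 0.073
- k = 5: 1 − 0.95^5 = 0.226; in favour, 1 − 0.975^5 = 0.119
- k = 14: 1 − 0.95^14 = 0.512; in favour, 1 − 0.975^14 = 0.298

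**Correlated tests, one route** (simulation of equicorrelated normal statistics, confirmed by numerical integration)

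| Measures | Counted | corr. 0 | 0.3 | 0.5 | 0.7 |
|---|---|---|---|---|---|
| 3 | either direction | 14% | 14% | 13% | 11% |
| 3 | favouring DAILY | 7% | 7% | 6% | 5% |
| 5 | either direction | 23% | 21% | 18% | 15% |
| 5 | favouring DAILY | 12% | 10% | 9% | 7% |
| 14 | either direction | 51% | 44% | 35% | 25% |
| 14 | favouring DAILY | 30% | 22% | 17% | 12% |

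The reference value is 5% in either direction, or 2.5% in DAILY's favour.

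**Both between-group routes.** Endpoint and change share the same endpoint data, so they overlap. With an assumed baseline-to-endpoint correlation r of 0.3 to 0.7, the two test statistics for one measure correlate at √((1 − r)/2). For three outcomes, either direction, the chance is then 24-26% at correlation 0 between outcomes and 19-20% at 0.7. The second route adds materially to the error even with the shortest list.

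**The stated aims side by side.** Design: not primarily to prove success, no power calculation. Limitations: the primary aim is proof whether symptoms improve. Abstract: efficacy. Under the first, a p-value is a by-product. Under the second, it is the evidence and its error needs control. The article does not say which reading governs.

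**The case against.** **This may be settled elsewhere.** An article condenses the full protocol, and a multiplicity rule or a designated primary analysis often stands in the analysis plan. That is fair for an omission. But the article itself fixes 0.05 for every calculation and itself states conflicting aims. A later plan could repair this only by departing from the published text.

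**The count of 14 is generous.** This stands in part. The article says separate diary scores can be created, not that nine between-arm tests will be run, and several parameters nearly duplicate one another (bedtime, time to go to bed, lights-off). Data Analysis also says diary data are reported descriptively, although the objectives and the Control Group section do plan to compare regularity between arms. The 14-measure figures are therefore conditional on all nine scores being tested. The figures for three and five do not depend on them.

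**Stronger readings that a reader might infer are not supported.**
- Fourteen measures by three routes would give 42 tests and, if independent, 1 − 0.95^42 = 88%. The third route ignores allocation and uses the Routine Variability Scores as predictor, so it is no randomized test of efficacy, and the other two routes are not independent.
- A chance finding for DAILY is not shown to be likely. On one route it is at most 30%, and that needs 14 independent measures.
- The article does not claim that efficacy has been proven. It states proof as an aim, and it also calls the study a pilot.
- Three primary outcomes in one place and two in another need not conflict, since drinking behavior can cover consumption and relapse.
- One might derive a sample size from the statement that 3-5 "subjects are involved in the study simultaneously" and conclude that power is too low. That needs assumptions about the recruitment period, constant occupancy and dropout that the article does not give, and it expressly forgoes power calculations. The point does not rest on it.

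**Regularity is a legitimate outcome.** It is a stated objective and the hypothesised mechanism. That stands, and it should be reported. It cannot stand in for benefit on drinking.

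**Conclusion.** The concern holds in moderate form. As written, any of several unadjusted primary tests could be read as success, and the article contradicts itself on whether that reading is intended. With no true effect, the error in either direction on one route is about 14% for three independent outcomes and 15-23% for five drinking measures. It is 25-51% if all nine diary scores are tested too. Restricted to results favouring DAILY, it is about half of these or a little more, against 2.5% for a single test. The size rests on the assumed correlations (0 to 0.7), two-sided tests, and how many measures are actually tested. The exact figure is uncertain, but each listed scenario is at least twice the nominal level. The ambiguity about the aim, and the fact that a regularity difference alone shows adherence, depend on none of these assumptions.

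**What to change.** 1. Name one primary between-arm comparison from data already collected. An example is TLFB-30 alcohol-free days at the final session, adjusted for the baseline value. The 30-day window matches roughly the 4-week application phase (30 against 28 days), not the whole six weeks. The choice of measure is the sponsor's, but it should be fixed before outcomes are looked at by arm.
2. Report one composite Routine Variability Score for weeks 3-6 as a mechanism or adherence outcome, and say that it cannot by itself support a claim of benefit.
3. Report all other outcomes, and the regressions that ignore allocation, as exploratory estimates with 95% confidence intervals. Replace the blanket 0.05 rule accordingly.
4. Align the Abstract, Measured Outcomes and Limitations with Design, so that the conclusion is preliminary estimates for the main trial.

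The cost is wording and a registry note, with no added patients, visits or instruments. The downside is that the sponsor gives up claiming efficacy from any other nominally significant test.

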## Study Hypotheses and Objectives

Our primary hypothesis is that a regular exposure to *Zeitgebers* stabilizes circadian behavioral rhythms and thereby reduces alcohol consumption and the risk of alcohol relapses in AUD patients. Accordingly, the primary objectives of the study are to determine whether the intervention program DAILY decreases day-to-day variations in behavior and reduces alcohol consumption and the relapse rate in AUD patients compared to those receiving control treatment. Furthermore, we hypothesize that the regular exposure to *Zeitgebers* contributes to the reduction of depressive symptoms and a subjective and physiological well-being in AUD patients, which in turn positively affects the primary objectives of the study. Accordingly, the secondary objective of the study is to ascertain whether the DAILY program supports the surrogate criterions of increased sleep quality, reduced depressive symptoms, increased self-efficacy expectations, and improved blood-values that are associated with harmful alcohol consumption. We also hypothesize, that additional psychoeducation about biological mechanisms in the development of AUD helps participants to complete their current therapy and maintain compliance. Therefore, as exploratory outcomes, we will investigate whether more participants of the intervention group accomplish the DAILY therapy than participants of the control group. Finally, we will assess whether the DAILY intervention has impact on the chronotype of the participants, although it is not a specific aim of our treatment to change it.

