**Figure 1 F1:**
[figure not shown]
Procedure of the DAILY study. Patients are screened and recruited by a member of the study staff. After 1 day at the earliest the participants sign the consent form. On this day, they are informed about the contents of the study; the contents discussed differ between intervention and control group. In addition, questionnaires are filled out and blood is drawn. During the week, a psychoeducation session takes place in which the contents and the aims of the study are deepened, further questionnaires (Table 1) are filled in, and a test diary is handed out to record times of daily actions which act as *Zeitgebers*. After at least 1 week, the diary is evaluated and a daily structure plan for regular exposure to *Zeitgebers* is worked out together with the test persons, to which they should adhere for the next 4 weeks. Subjects in the control group are not given instructions on how to structure their daily routine but are still asked to complete the diary. At least one telephone appointment is made for the time the subjects fill out the diaries to maintain compliance. After 4 weeks, there will be a final personal appointment where the diaries will be collected, all questionnaires will be repeated, and blood will be drawn again.

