### Recruitment

In order to facilitate recruitment, a logo was designed for the DAILY study, which has a high recognition value for the test persons and underlines the official character of the study (Figure 2). After screening for eligibility, participants are recruited during their clinical stay at either the specialist ward or the outpatient clinic for addiction disorders. A member of the study staff addresses the candidates personally and finds out whether there is in principle interest in participating in a concomitant therapy study for AUD patients. Candidates are given at least 1 day to consider. In the event of positive feedback, they are allocated to either the intervention or control group.

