### Intervention Group

#### Week 1: Psychoeducation and Test Diary

After baseline assessments, a few days later in the same week, the test persons participate in individual 1-h psychoeducation sessions about circadian clocks and their effects on health and psychiatric disorders, such as addiction and depression. The scientific content is communicated in simple language. Firstly, the participants get explained that circadian rhythms can be found virtually everywhere in nature and that they have impact on essentially all physiological processes, including sleep-wake cycles, hunger, digestion, wound healing, cellular functions, and molecular processes. A focus is on their involvement in neurobiological systems, such as reward, addiction networks, and behaviors. During the session, the test subjects are led to understand how important regular daily routines are for mental and physical health. Therefore, the study assistant emphasizes the importance of certain environmental cues that can serve as *Zeitgebers*, such as light and food. Together with the participants, the impact of light on sleep is discussed and how light can be avoided at late hours (e.g., by stopping the use of mobile phones, watching TV, or playing computer games after sunset or by using blue-light filters). Furthermore, the importance of regular mealtimes is discussed as food is an important *Zeitgeber* for many organs, including brain areas involved in the development of addiction. At the end of this session, the study assistant hands out a circadian diary (Supplementary Table 1), which the participant is asked to fill out for 1 week. With the help of the diary, data on times of meals, snacks, activity times, sleep duration, sleep quality, mood, and alcohol craving are collected on a daily basis. At this point in time, the test persons do not yet receive any concrete instructions as to when they should execute activities. Rather, they are instructed to use the following days to see if they can recognize certain temporal patterns in their own behavior and to consciously follow these patterns. Filling out the test diary serves on the one hand to create an awareness of their own daily rhythms. Besides, it gives the test persons the opportunity to familiarize themselves with the filling out of the diary. On the other hand, the data obtained on eating and sleeping times can be used in the next session as a basis for drafting a daily structure plan.

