## Discussion

The DAILY intervention is a new concomitant treatment approach for patients suffering from AUD, which is based on the strengthening of the patients' circadian system with the targeted use of *Zeitgebers* such as sleep, meal, and activity times. The timing for the regular use of the *Zeitgebers* is personalized and tailored to the individual patients including both their genetically imprinted circadian characteristics as well as individual social obligations, such as working hours. Hence, the personalized design should therefore make the strengthening of physiological rhythms as effective as possible by taking individual characteristics into account on the one hand, and on the other hand as easy to implement as possible by including environmental constraints. Each individual is determined by a genetic constellation that defines optimal times for sleeping, eating and physical exertion (e.g., sports). In turn, these specific actions serve as *Zeitgebers* for the circadian system. Consequently, the circadian clock and the *Zeitgebers* form a positive feedback system, which leads to mutual reinforcement. Thus, this bidirectional influence can be used to strengthen and stabilize circadian clocks. Our therapy makes sure that actions serving as *Zeitgebers* are performed at the same time on all days. This preserves the circadian system from repeated shifts and ensures that a fixed phase relationship among physiological processes, and thereby endogenous synchronization, can be established. However, there are many individuals who are subject to social times that they cannot completely elude in everyday life and which may change between work and work-free days. The primary focus of our study is to test whether AUD patients benefit from increased regularity of *Zeitgeber* exposure which requires adherence to the same schedule on workdays and workfree days. Thus, our therapy bears the risk of a permanent misalignment or sleep deprivation for some participants. Therefore, if the endogenous rhythms of the test subjects, who are not in the position to choose their sleeping times on most days of the week, deviate more than 2 h from constrained social times, they are advised to adjust their biological time using light therapy to avoid chronic misalignment with the environment. Thus, our therapy ensures endogenous alignment of rhythms and additionally counteracts the so-called social jetlag, which is also associated with increased alcohol consumption (68, 69). However, if internal and external rhythms are found to be extremely different, subjects may not be suitable for this study.

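### The set labelled intention-to-treat is defined by completing a first-week diary that follows allocation and arm-specific sessions, and the same paragraph contradicts that definition

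*Protocol article*

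**What the plan says.** The Data Analysis section of the protocol article states: "Data analysis will be performed according to intention-to-treat analysis (ITT) rules". It spells this out with the rule that "all subjects who completed the questionnaires of the first session and the 1st week of the diaries are included in the analysis", and describes imputation for what those participants are missing afterwards. It then treats as dropouts those who withdraw consent and have no baseline measurements, and ends: "All other subjects regardless from the study condition will be analyzed according to ITT".

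The timing is set out elsewhere in the article:

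- **Recruitment:** once a candidate has agreed to take part, "In the event of positive feedback, they are allocated to either the intervention or control group".
- **Figure 1 caption:** on the day of consent, "the contents discussed differ between intervention and control group".
- **Intervention Group, Week 1:** a one-hour circadian psychoeducation session follows a few days later. "At the end of this session, the study assistant hands out a circadian diary", to be kept for one week.
- **Control Group:** the order of sessions and diary is the same, with different content.

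**The concern.** An ITT set is fixed by randomisation. This one is fixed partly by something participants do afterwards, once the arms have been treated differently. If the people who fail to complete a diary week differ in number or prognosis between arms, the groups compared are no longer the groups randomised.

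The article itself gives reasons to take this seriously. Study Hypotheses and Objectives proposes that the psychoeducation "helps participants to complete their current therapy and maintain compliance", and the Discussion repeats that expectation. The Outlook section warns that diaries are prone to non-completion and data gaps. Regularity of daily routine is a primary outcome, and completing a diary plausibly goes with it.

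The condition can also discard usable data. Drinking is measured by AUDIT, EuropASI and TLFB at the first and last sessions (Table 1), and none of these needs a first-week diary.

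**Working it through.** The article states no sample size, dropout rate or relapse rate, so there is no figure to reproduce. The check is on order of events and on wording, followed by an illustration.

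**Order of events**

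1. Allocation (Recruitment).
2. Consent day: baseline questionnaires, with content already differing by arm (Figure 1 caption).
3. Psychoeducation in the DAILY arm, other topics in control (Intervention Group, Week 1; Control Group).
4. First-week diary. DAILY participants are also told to look for their own daily patterns and follow them. Controls are asked only to fill the diary in carefully.
5. Entry to the analysis set, which requires steps 2 and 4.

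Step 5 depends on step 4, and step 4 comes after steps 1 and 3. The set is a modified ITT set.

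**The two sentences side by side**

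| Participant | Diary rule | Closing sentence |
|---|---|---|
| Baseline and first-week diary done, leaves later | In | In |
| Baseline done, no first-week diary | Not in | In |
| Consent withdrawn, no baseline | Not in | Dropout |

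The second row is the conflict. Two analysts could build different datasets from this one paragraph.

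**Illustration (all rates assumed)**

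Let *p* be the relapse rate of everyone randomised, equal in both arms (no true effect). Let *pL* be the relapse rate of those without a first-week diary, also equal in both arms, and *d* the share left out. The relapse rate in those analysed is (*p* − *d*·*pL*) / (1 − *d*).

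Take *p* = 0.40 or 0.50 and *pL* = 0.70 or 0.90. Differences are DAILY minus control, so a positive value makes DAILY look worse.

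| Left out, DAILY v control | Smallest difference (*p* = 0.50, *pL* = 0.70) | Largest difference (*p* = 0.40, *pL* = 0.90) |
|---|---|---|
| 10% v 10% | 0 | 0 |
| 5% v 15% | 0.465/0.95 − 0.395/0.85 = 0.489 − 0.465 = +2.5 points | 0.355/0.95 − 0.265/0.85 = 0.374 − 0.312 = +6.2 points |
| 5% v 25% | 0.465/0.95 − 0.325/0.75 = 0.489 − 0.433 = +5.6 points | 0.355/0.95 − 0.175/0.75 = 0.374 − 0.233 = +14.0 points |

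Swapping the arms reverses the sign. With equal loss and equal prognosis of leavers, the difference is nil.

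**The case against.** **Wording.** The diary sentence says that completers are included. It does not say that nobody else is, and the closing sentence can be read as the wider rule. That is fair, and it is why the conflict is part of the point. But the diary sentence is introduced as the explanation of what ITT means here, and imputation is described for data missing after that week. The wider reading therefore cannot be taken as settled. Nor is this detail left to a fuller document: the rule is stated, and stated in two ways.

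**Pilot status.** The Design section says the trial is a pilot that does not mainly aim to prove efficacy. This lowers the stakes. Between-arm tests at the 0.05 level are still planned under an ITT label.

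**Stronger readings that the article does not support**

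- A reader might infer that early leavers do differ by arm. No dropout figures are given, so this is a risk only.
- A reader might infer a false benefit for DAILY. The article's own retention hypothesis points to fewer leavers in DAILY, which under the assumptions above would count against it.
- The Discussion remarks that "if internal and external rhythms are found to be extremely different, subjects may not be suitable for this study", and a reader might see a second exclusion acting in one arm. The remark states no analysis exclusion. The mismatch is considered when the daily plan is drawn up in Week 2, after the test diary, and participants who have reached that stage with the diary completed are kept whatever happens later.
- A reader might infer that the earliest losses vanish from the dropout comparison. Neither Measured Outcomes nor Data Analysis restricts that comparison to diary completers.

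**Conclusion.** The point stands as a mislabelled and internally inconsistent analysis set. It rests on the stated order of events and on two sentences of one paragraph, and needs no assumed rate. Inclusion by the diary rule depends on behaviour after randomisation and may differ by arm.

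The size and direction of any resulting bias cannot be known from the article. The range of 2.5 to 14.0 percentage points shows only what unequal loss of 5% against 15% to 25% could do if leavers relapse at 70% to 90% against 40% to 50% overall. It is not an estimate for this trial. The definition should be corrected before any comparison by arm is made.

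**What to change.** - Delete the first-week-diary condition. Define the ITT set as all randomised participants who signed consent and did not withdraw consent to data use, analysed in the arm allocated. The signature has to be named because Recruitment places allocation at the point of agreement, while the form is signed in the first week.
- Reword or remove the closing sentence so that one rule remains.
- Analyse AUDIT, EuropASI and TLFB in that set whether or not a diary exists.
- Report any diary-completer set only as a labelled modified-ITT or sensitivity analysis, with exclusions by arm.

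The cost is a change of analysis wording and somewhat more missing data. One difficulty remains: a participant with no diary at all has no Routine Variability data of their own from which to impute that outcome. The plan should say how such participants are handled for it.
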